We will use a variety of computational/statistical approaches to assess the extent to which expression of various genes and their associated metabolic/signaling pathways in duodenal biopsies in children with celiac disease, Crohn’s disease, and EE overlap or differ. We will approach this using several statistical methods; PCA plots; Venn diagrams of the differently expressed genes between celiac disease vs. controls, EE vs. controls, and Crohn’s disease vs. controls; and associated pathway analyses. A significant overlap in pathways could provide insights into pathogenesis and new treatment approaches, such as tight junction modulation, which are in development for celiac disease [57]. Gene signatures distinct for EE would further provide a promising source of future therapeutic targets and initial tissue-level validation of promising biomarkers that would be useful for predicting growth and powering studies to test future interventions against EE. We also plan to compare proximal small intestinal duodenal biopsies with distal ileal biopsies in the Crohn’s cohort to determine how well the duodenal pattern of gene expression reflects the ileum.

Analyses of biopsies from both Crohn’s disease and celiac disease patients will also provide us the opportunity to test for the relationship between the microbial community and gene expression signatures. We will test for associations between taxa of the duodenal microbial community and specific clinical and gene expression metadata using Multivariate Analysis by Linear Models (MaAsLin) as has been described in prior studies [27, 49, 50]. A comprehensive description of this analysis method has been published online [58]. In short, for each arcsine square root transformed microbial feature, a model is selected from metadata using gradient boosting (gbm package [59]). Covariates in the selected model are then evaluated controlling for potential confounders using a general linear model. Additionally, confounders will also be assessed via construction of a causal pathway. Multiple comparisons over factor levels will be adjusted using a Bonferroni correction, and multiple hypothesis tests over all clades and metadata will be adjusted with a false discovery rate [60].

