All significant (α < 0.05) associations will be investigated in the analysis: clinical phenotype (including severity of wasting), stool and duodenal enteropathogen burden, endoscopic inflammation, histologic severity, and selected duodenal differentially expressed genes such as IFN_γ_ and APOA1. We plan to control for age, gender, and body mass index (as a measure of nutritional status) in our analysis. These analyses will identify specific duodenal microbial taxa associated with differences in IFN_γ_ and/or APOA1 gene expression across the three disorders tested; EE, Crohn’s disease, and celiac disease.

Next, analyses of mRNAseq performed on biopsy tissues will be carried out using polyA-RNA selection, fragmentation, cDNA synthesis, adaptor ligation, and library preparation with TRUSeq RNA Sample preparation (Illumina, San Diego, CA, USA). Paired-end 75 bp sequencing will be performed using the Illumina HiSeq 2000 in the CCHMC NIH-supported Digestive Health Center with a minimum depth of 20 million reads per sample. Reads will be aligned using TopHat [61]. The aligned reads will be quantified by Avadis NGS software (Version 1.3.0, Build 163,982 Strand Scientific Intelligence, Inc., San Francisco, CA, USA) using Hg19 as the reference genome and RPKM as an output. The DESeq algorithm will be used for RPKM normalization within Avadis NGS software. Two more recently applied alternative approaches for quantification will also be assessed using kallisto [62] and eXpress [63].

For RNA-Seq expression and gene enrichment analysis samples will be stratified into specific clinical subgroups including control, EE, celiac disease, and Crohn’s disease. For some analyses the EE group will be further sub-divided into those with an identified infection (e.g. *Giardia, H. pylori*) and those without an identified infectious etiology. In addition, we plan to stratify the Crohn’s patient samples by their location to assess expression differences between proximal (duodenal) and distal (ileum) small bowel expression.

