Other potential sub-stratification of the EE group will be based on CRP level, histologic severity, response to rotavirus infection (by measuring rotavirus IgA levels), and weight/height outcomes. Differentially expressed genes of the above stratified groups will be determined by the Audic Claverie method using the Benjamini-Hochberg false discovery rate correction (FDR 0.05) and analyzed for fold change differences. Normalized intensity values will be used for patterns of gene expression. Pearson correlation based on trend and rate of change will be performed for IFN_γ_ and APOA1 gene expression across defined groups for correlation coefficient of 0.98 < |r| < 1.

ToppGene [64], ToppCluster [65], and IPA (Ingenuity Systems) software will be used to test for functional annotation enrichment analyses of upstream regulators, immune cell types, pathways, phenotype, and biologic functions. Functional annotation enrichment analyses for immune cell type enrichments will be characterized using the Immunological Genome Project data series through ToppGene. Visualization of the functional networks will be obtained using Cytoscape v.3.02 [66].

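### The MaAsLin step selects covariates by boosting and then tests them, on the natural reading in the same children; the article leaves open whether its false discovery rate adjustment counts the pairs that boosting dropped

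*Protocol article*

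**What the plan says.** All of this stands in the Data analysis plan of the protocol article.

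- **Selection, then testing.** The analysis takes one taxon at a time, after transformation. The article then states: "a model is selected from metadata using gradient boosting (gbm package [59]). Covariates in the selected model are then evaluated controlling for potential confounders". The tests come from a general linear model. No selection threshold, hold-out sample or correction for selection is described. Fuller detail is left to a cited online description.
- **Multiplicity.** Comparisons between the levels of a factor get a Bonferroni correction. For the wider family the article states: "multiple hypothesis tests over all clades and metadata will be adjusted with a false discovery rate". No FDR level is given here, and the text does not say whether pairs dropped by boosting belong to the family.
- **Significance.** "All significant (α < 0.05) associations will be investigated in the analysis". This is not labelled as a raw or an adjusted value. The factors that follow cover wasting, pathogen load, endoscopic and histologic findings, and genes such as IFNγ and APOA1, with control for age, gender and body mass index.
- **The only numeric FDR level** belongs to RNA-Seq differential expression: "using the Benjamini-Hochberg false discovery rate correction (FDR 0.05".

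**The concern.** A linear-model p-value is calibrated for a covariate chosen without looking at the outcome. Here a covariate reaches the linear model because it already helped to predict that taxon. If the same children are used for both steps, small p-values are over-represented under the null.

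An FDR procedure can absorb this if the dropped pairs stay in its denominator. A dropped pair produces no linear-model p-value, however, so an analyst who adjusts the p-values that the procedure produces would leave those pairs out.

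At stake are the links between duodenal taxa and IFNγ, APOA1 and disease severity, for which this is the method that the plan names. Chance associations could be reported as microbe–gene findings.

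**Working it through.** The article states no error rate for this step, so there is no figure to reproduce. The check is a simulation.

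**Inputs from the article.** 50 SEEM children with duodenal samples (Sample size), and 30 celiac and 30 Crohn's children (Study settings and participants). The three disorders give 50 + 30 + 30 = 110; EE alone gives 50. Three adjustment covariates; nominal level 0.05.

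**Assumptions.** 20 candidate metadata variables (10 and 40 also tried), 50 taxa and independent Gaussian data. Boosting used 100 stumps, shrinkage 0.1 and bag fraction 0.5. Covariates were kept if their relative influence exceeded 1× the mean (moderate), 2× the mean (tight) or 1% (very lenient). Selected covariates were then tested by ordinary least squares with the three adjustment covariates forced in, followed by Benjamini-Hochberg at 0.05.

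**Results, 400 replicates per row**

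| n | Cut-off | True pairs | Mean kept of 20 | Null rejection, selected | FDR, tests run only | FDR, all pairs | FDR, no selection | FDR, split sample |
|---|---|---|---|---|---|---|---|---|
| 110 | 1× | 0 | 8.74 | 0.117 | 0.160 | 0.070 | 0.030 | 0.048 |
| 110 | 2× | 0 | 1.39 | 0.314 | 0.680 | 0.065 | 0.065 | 0.050 |
| 110 | 1× | 10 | 8.33 | 0.121 | 0.138 | 0.057 | 0.050 | 0.055 |
| 110 | 2× | 10 | 1.42 | 0.322 | 0.458 | 0.053 | 0.051 | 0.043 |
| 50 | 1× | 0 | 8.47 | 0.124 | 0.225 | 0.113 | 0.048 | 0.048 |
| 50 | 2× | 0 | 1.60 | 0.325 | 0.635 | 0.090 | 0.058 | 0.050 |

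The simulation standard error at 0.05 is √(0.05 × 0.95 / 400) = 0.011. With no true pairs, the FDR is the chance of any rejection. The last two columns hold the level within simulation error, so selection on the tested data is the cause.

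**Sensitivity to the assumptions** (60 to 100 replicates, n = 110, no true pairs)

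- Above 1% influence: 18.85 of 20 kept, null rejection 0.056, FDR 0.067 with either family.
- 1× mean, 10 metadata: null rejection 0.103, FDR 0.05 over the tests run.
- 1× mean, 40 metadata: null rejection 0.128, FDR 0.20 over the tests run and 0.083 over all pairs.

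A separate null simulation with the 1× and 2× cut-offs gave null rejection of about 11–12% and 28–35%. The chance of a false discovery was about 9–19% and 49–67% over the tests run, and about 3–9% over all pairs.

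Another kept a fixed number of covariates (top 1, 3 or 5 of 8, 12 or 20; 40 taxa; n = 110). Null rejection ran from 8% (top 5 of 8) to 43% (top 1 of 20). The chance of a false discovery over the tests run went from 4% to 82%. Over all pairs it was about 3–9%.

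**Why the denominator matters**

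1. Counting every pair and treating dropped ones as non-significant, the share of null pairs below 0.05 is (rejection among selected) × (share kept). At n = 110 this is 0.117 × 8.74/20 = 0.051 and 0.314 × 1.39/20 = 0.022. The raw p-values look normal or better once the dropped pairs are counted.
2. The first Benjamini-Hochberg threshold for m tests is 0.05/m. Over all pairs, m = 50 × 20 = 1,000 and the threshold is 0.00005. Over the tests run with the 2× rule, m = 50 × 1.39 = 69.5 and it is 0.00072, about 14 times looser. With the 1× rule, m = 50 × 8.74 = 437 and it is 0.00011, about 2.3 times looser.
3. At n = 50 some excess remains even over all pairs (0.113 and 0.090). A likely reason is that the selected covariates absorb noise, so the residual variance is understated, more so in small samples.

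**The case against.** The strongest reply is that the article already calls for adjustment over all clades and metadata. Read broadly, that is the full family, and at 110 children the FDR then comes out at 0.053–0.070. This stands. A reader might infer from the select-then-test order that the plan fails to hold its stated false discovery rate. The documents do not support that: no numeric level is stated for MaAsLin, the 0.05 belongs to the RNA-Seq analysis, and under the broad reading the rate is near nominal.

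Three further points also have weight. The article condenses a method described elsewhere, and the cut-off, the family and any sample splitting may be set out there; use of the same children is the natural reading, not an explicit statement. The size of the effect rests on assumed settings, and some of them are harmless. The step is also exploratory: the sample-size endpoint does not depend on it, and gnotobiotic mouse experiments are planned to test causality.

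What the reply does not remove is the order that the article itself sets, selection and then ordinary testing. The phrase on the family does not settle how pairs without a p-value are treated, and the 0.05 criterion is not tied to the adjusted value.

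**Conclusion.** The concern holds in a limited form. The raw p-values of boosting-selected covariates are too small: null rejection is about 11–35% at nominal 5% under moderate to tight cut-offs, and near nominal (0.056) under a very lenient one.

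In the main runs at 110 children, the FDR is 0.14–0.68 if only the tests run are adjusted and 0.053–0.070 if every clade-by-metadata pair counts. At 50 children the figures are 0.225–0.635 and 0.09–0.11, so in an EE-only analysis about twice the nominal rate can remain even with the full family.

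These sizes rest on the assumed cut-offs, numbers of metadata and taxa, and independent Gaussian data, and on selection and testing sharing the same children. The primary IFNγ/APOA1 comparison is not affected.

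**What to change.** 1. State that Benjamini-Hochberg is applied over every clade-by-metadata pair, with p = 1 entered for each pair that boosting did not select, and give the FDR level.
2. State that the 0.05 criterion for the associations to be investigated refers to the FDR-adjusted value, not to a raw p-value.
3. For any MaAsLin analysis confined to the EE children (about 50), add a sensitivity analysis with one pre-specified linear model per taxon, using the factors and adjustment covariates that the Data analysis plan already lists, without the boosting screen. In the simulations this model held the level at n = 50 (0.048–0.058).

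The cost is a few sentences, a changed denominator and one extra model run. The downside is fewer reported associations. The boosting step can stay.

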**Fig. 1 Fig1:**
[figure not shown]
Conceptual framework for hypothesis testing in SEEM. The severity of clinical phenotypes in Matiari children with wasting and suboptimal response to nutritional rehabilitation will highly correlate with the histopathological appearance of duodenal biopsies; duodenal and fecal dysbiosis; perturbation of duodenal gene expression profiles; systemic biochemical profiles; and children’s genotypes. The image in the top right panel demonstrates the histological changes observed in the small intestine as environmental enteropathy progresses. Note: *L:R* lactulose:rhamnose ratio, *EE* environmental enteropathy, *GI* gastrointestinal, *HLA* Human Leukocyte Antigen

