### Histopathologic, immunohistochemistry and transcriptomic work up of biopsy specimens

We hypothesize biopsies from children whose endoscopic workup does not reveal a clear malabsorptive pathology, such as celiac disease, will likely demonstrate advanced features of EE. Previous studies suggest at least two factors contribute to EE: (i) chronic T-cell mediated intestinal damage and (ii) perturbations in microbial community structure/function [13, 48]. Recognizing that our sample will be restricted to children whose wasting (WHZ ≤ − 2) is refractory to nutritional intervention, we will comprehensively assess biopsy specimens to better understand the pathology of the proximal small intestinal mucosa in EE.

One such previous attempt utilizing duodenal biopsies compared malnourished children in Gambia with healthy UK age-matched children to better understand the pathogenesis underlying this disorder [10]. This study was, however, restricted to morphometric and targeted immunohistochemical analyses for immune cell markers, and did not investigate gene expression associated with the absorptive epithelial layer more broadly. The authors concluded that cell-mediated Th1 response might impair mechanisms of oral tolerance and drive progressive growth failure despite intensive nutritional intervention [10]. Therefore, we propose to supplement routine clinical histologic morphometric analyses with (i) targeted staining to characterize immune cells and the epithelial layer (working with the UVa Biorepository and Tissue Research Facility (BTRF) we have recently established a protocol for triple color immunohistochemical staining), (ii) RNA-Seq analyses to capture a more inclusive EE gut gene expression signature, (iii) gut biopsy DNA-based 16S rDNA characterization of the biopsy-adherent bacterial communities, and (iv) perform microbe:gene association studies (Fig. 3). We hope that these data will provide new insights into both disease pathogenesis and treatment, as well as gut-derived circulating biomarkers for disease severity, which may be assayed in future studies using the banked sera from the larger 400 patient SEEM cohort.

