### Data analysis plan

This study will result in a vast dataset containing sociodemographic and anthropometric information, as well as biomarkers found in urine, stool, and blood, and endoscopic biopsy results highlighting histopathologic features of both diseased and healthy gastrointestinal tracts.

The WHO Child Growth Standards (WHO Anthro, Geneva, Switzerland) [51] will be used to calculate z-scores, and assess growth both as continuous measures of height-for-age z-score (HAZ), weight-for-age z-score (WAZ) and weight-for-height z-score (WHZ); and as categorized variables of stunting as HAZ < − 2 SD (standard deviation), underweight as WAZ < − 2 SD and wasting as WHZ < − 2 SD. Participant descriptive statistics will be presented as means (standard error, SE) and as frequencies (percentages) for continuous and categorical outcomes, respectively. We will also perform simple linear regression for a specific time point and mixed-effects modeling analysis for repeated measurements to study change in growth trends over the follow-up period.

Mass spectrometry will be used to determine serum and urine bile acid profiles and serum non-essential fatty acid levels, and amino acid profiles. In addition, the cellular fraction of the obtained blood will be utilized for DNA extraction and high-throughput genotyping using Infinium HumanOmniExpressExome [52]. Genotyping will also be used to determine HLA typing of the individual and their associated genetic ethnicity. Given the similarities between EE and celiac disease, it will be of interest to determine whether there is also a common HLA genotype associated with EE [53]. Both environmental and genetic factors [54], play roles in gut microbial composition, therefore, we will control for genetic variants (i.e. HLA [55], FUT2 [56]) in some of the planned microbial and gene expression analyses.

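### The microbial association models test severity of wasting while always adjusting for BMI, so that test is largely adjusted for itself

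*Protocol article*

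**What the plan says.** The Data analysis plan describes MaAsLin models in which each transformed microbial feature is the outcome. Metadata are selected by gradient boosting, and the selected covariates are then evaluated in a general linear model that controls for potential confounders. A causal pathway is also to be constructed to assess confounders.

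Three consecutive statements then fix what is tested, what is adjusted for and what is sought:

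- Factors investigated: "clinical phenotype (including severity of wasting), stool and duodenal enteropathogen burden, endoscopic inflammation, histologic severity", and selected genes such as IFN-gamma and APOA1.
- Adjustment: "We plan to control for age, gender, and body mass index (as a measure of nutritional status) in our analysis".
- Target: "These analyses will identify specific duodenal microbial taxa associated with differences in" IFN-gamma and/or APOA1 expression across EE, Crohn's disease and celiac disease.

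Four other places bear on this:

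- The Data analysis plan defines wasting as WHZ below −2.
- The section on work-up of biopsy specimens says of the EE group that "our sample will be restricted to children whose wasting" (WHZ at or below −2) has not responded to nutritional intervention.
- The Background describes undernutrition as something EE contributes to, through inflammation and malabsorption.
- The Fig. 1 caption states the hypothesis: "The severity of clinical phenotypes in Matiari children with wasting and suboptimal response to nutritional rehabilitation will highly correlate with the histopathological appearance". The tissue meant is the duodenal biopsy, and the caption names dysbiosis and gene expression as further correlates.

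**The concern.** Severity of wasting is an exposure in these models, and BMI is a fixed covariate in them. Both express weight relative to height. A model containing both asks whether WHZ carries information about a taxon among children with the same BMI, which is a much narrower question than whether more severely wasted children have a different duodenal community. The Fig. 1 hypothesis on phenotype severity and dysbiosis needs the second question.

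A related problem arises where the models compare disorders. BMI is then connected to the way EE children entered the biopsy group, and on the article's own account it lies downstream of EE. Adjusting for such a variable is not plain confounder control.

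At stake is the ability to detect links between wasting severity and duodenal taxa in a biopsy group of about 50 children, with a false discovery rate correction over all clades and metadata.

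**Working it through.** The plan gives no figure for this choice, so there is none to reproduce. The check has two parts.

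**1. Severity of wasting as the exposure**

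Inputs: the correlation r between BMI and WHZ among endoscoped children is not in the documents, and 0.85 to 0.95 is assumed. Age and sex terms are left aside.

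Formulas: the share of wasting variance left after BMI adjustment is 1 − r². The variance inflation factor is VIF = 1/(1 − r²), and the standard error grows by √VIF. A test with 80% power without BMI (two-sided 0.05) keeps power Φ((1.96 + 0.84)·√(1 − r²) − 1.96), if the coefficient itself does not change.

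| r | 1 − r² | VIF | SE multiplier | 80% power becomes |
|---|---|---|---|---|
| 0.85 | 0.2775 | 3.60 | 1.90 | 31% |
| 0.90 | 0.19 | 5.26 | 2.29 | 23% |
| 0.95 | 0.0975 | 10.26 | 3.20 | 14% |

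The assumed range was checked by simulating WHZ and BMI at a fixed age among children with WHZ below −2, with assumed height and weight relations. The correlation was 0.92 to about 1.0, so the table is not extreme for continuous WHZ at one age.

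Severity may instead be entered as a category, since Study settings and participants separates moderate from severe malnutrition at WHZ −3. I simulated normal WHZ with mean −1.5 or −2.5 and SD 1, cut off at −2, and kept r at 0.85 to 0.95. The correlation of the severe/moderate indicator with BMI was then 0.69 to 0.77 in absolute value, giving a VIF of 1.9 to 2.5 and an SE multiplier of 1.4 to 1.6.

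**2. Disease group as the exposure**

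The relevant statements, side by side:

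- EE children are biopsied only if low weight-for-height persists (work-up of biopsy specimens).
- The US celiac, Crohn's and control groups have no WHZ or BMI criterion and may be of any age under 11 years (Study settings and participants).
- Undernutrition is a postulated result of EE (Background).

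BMI is therefore related to EE membership through selection and, if the postulate is right, through the disease. How far the groups differ depends on the BMI of the comparators, which is not given. As an illustration, take 25 EE children and 30 comparators, with a comparator mean z-score between −1 and 0 and a correlation of 0.8 to 1.0 between the selection score and the BMI score. The R² of group on BMI is then 0.36 to 0.73, and the VIF is 1.6 to 3.7. If the comparators are themselves undernourished, the figures are smaller.

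A VIF measures lost precision only. It does not show the direction of any bias from conditioning on a selection-related or downstream variable.

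**The case against.** The strongest reply is about scope. The BMI sentence closes the MaAsLin description, and the stated target there is the association of taxa with IFN-gamma and APOA1 expression. Adjusting a taxon–gene association for nutritional status can be defended, because wasted Pakistani children and US children are pooled and nutritional status may confound the link. The plan also promises a causal pathway, the usual tool for separating a confounder from a mediator. Because covariates are selected for each microbial feature, wasting severity need not appear in every model that contains BMI.

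Much of this stands. A reader might infer that BMI adjustment removes the study's main contrasts, but the documents do not support that. The primary IFN-gamma/APOA1 comparison in Sample size and the stratified expression analyses later in the Data analysis plan carry no stated BMI term. A reader might also infer three further things:

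- *That BMI separates the groups by design.* No weight criterion is set for the US groups, and the WHZ above 0 rule belongs to the Matiari controls, who are not biopsied.
- *That the results are biased toward the null.* The direction is not established.
- *That BMI is entered unstandardised.* The article does not state its scale.

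What the reply does not answer is the wasting-severity test. It is named as a test, the BMI sentence follows without condition, and the causal-pathway step is not said to override it.

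**Conclusion.** The point holds for the MaAsLin association models. Followed as written, they test severity of wasting conditional on a near-duplicate of it. Under the assumed correlations of 0.85 to 0.95, the standard error is 1.9 to 3.2 times larger for continuous WHZ and about 1.4 to 1.6 times larger for a moderate/severe coding. The correlations are assumptions, and the size moves with them.

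For EE against Crohn's or celiac disease within these models the finding is weaker: BMI-adjusted contrasts may be attenuated or depend on limited overlap, by an amount and in a direction that the documents do not determine. For taxon–gene associations, nutritional adjustment remains a legitimate option. The primary comparison of EE with controls is not affected.

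**What to change.** Amend the adjustment sentence in the Data analysis plan to distinguish three cases:

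- **Severity of wasting as the exposure:** adjust for age and sex, and do not include BMI.
- **Disease group as the exposure:** make the age- and sex-adjusted result the main one. Show nutritional-status adjustment as a labelled sensitivity analysis, using an age-standardised z-score because comparators may be of any age under 11 years.
- **Taxon–gene associations:** keep nutritional-status adjustment where the planned causal pathway supports it, and report results with and without it.

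The cost is a short change of text and one extra model run. No new data are needed.

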### Sample size

Participants will be recruited from our prospective cohort. Based on our phase 1 cohort [14], we anticipated that the cohort of 50 SEEM patients, with duodenal samples collected by endoscopy, will include at least 20 without a single identified treatable infection, i.e. identified *Giardia* or *H. pylori* infection*.* The primary endpoint guiding our sample size estimate will be the anticipated differences in duodenal IFN_γ_ and APOA1 gene expression between subjects with EE and healthy controls. We anticipate that induction of IFN_γ_ gene expression will be associated with a reduction in APOA1 gene expression as per a recent study on Crohn’s disease [27] and that of Bragde et al. on celiac disease [28]. In the Crohn’s study, the mean (SD) Reads Per Kilobase per Million Mapped reads (RPKM) IFN_γ_ gene expression at diagnosis was equal to 1.86(2.7) in patients with Crohn’s, and 0.33(0.38) in healthy controls. The mean (SD) RPKM APOA1 gene expression at diagnosis was 927(1469) in patients with Crohn’s, and 3012(3080) in healthy controls. We anticipate similar differences between EE and healthy controls in our study. Based on these results, 30 healthy controls and 25 EE subjects without a specific treatable infection will provide 90% power to detect such a difference with α = 0.05. The secondary endpoint will be to perform an undirected analyses to capture the overall gene and signatures that are different between described groups. Based on previously published data for RNA-Seq samples size estimation [29], if we estimate a coefficient of variation of counts of 0.4 as was observed in 90% of the genes in a range of human studies, alpha of 0.05 and power of 0.8, a sample size of 20 per group will be needed.

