To date, studies of the role of the gut microbiota in the pathogenesis of environmental enteropathy (EE) have been limited by challenges in obtaining well-preserved upper GI communities from individuals whose disease status has been confirmed by endoscopic evaluation. To define the relationship between the configuration of the fecal microbiota and histopathologically-defined EE in the SEEM cohort, we will first generate Random Forests-derived models of normal gut microbial community development; this will be done using bacterial V4-16S rDNA and shotgun sequencing datasets of community DNA respectively, generated from monthly fecal samples collected for the first 2 years of life from well nourished children (WHZ > 0 and HAZ > -1) of the Matiari birth cohort. These culture independent methods will be applied to duodenal biopsies and aspirates collected at endoscopy from children who failed to respond to nutritional intervention in order to identify bacterial strains (and members of other domains of life and their viruses) in the proximal small intestine whose representation/abundance are correlated with severity of EE (as assessed by histologic grading [22]). Bacterial strains will be cultured and their genomes sequenced. BugFACS [47] will also be performed on fecal samples obtained from children at the time of endoscopy to identify bacterial strains whose targeting by mucosal IgA is correlated with pathologic features of disease. These results will be further contextualized using data obtained from (i) multi-omics analysis of duodenal specimens from the same children that will be performed at CCHMC and WUSTL (RNA-Seq, metabolomics/proteomics), plus (ii) results of EE biomarker analyses performed on contemporaneously collected plasma and fecal specimens.

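### Potential EE sub-strata for gene expression would cut graded measures (CRP, histology, rotavirus IgA, growth) where a per-gene slope uses the same data with more power

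*Protocol article*

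**What the plan says.** All references are to the protocol article.

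- **Data analysis plan, strata.** After dividing the EE group by identified infection, the article adds "Other potential sub-stratification of the EE group will be based on CRP level, histologic severity", followed by rotavirus IgA response and weight/height outcomes. It gives no cut-points and no number of strata.
- **Data analysis plan, test.** "Differentially expressed genes of the above stratified groups will be determined by the Audic Claverie method", "using the Benjamini-Hochberg false discovery rate correction (FDR 0.05").
- **Sample size.** The biopsied group is described thus: "we anticipated that the cohort of 50 SEEM patients, with duodenal samples collected by endoscopy", of whom it says the cohort "will include at least 20 without a single identified treatable infection". The power statement uses 25: "30 healthy controls and 25 EE subjects without a specific treatable infection will provide 90% power". For the undirected RNA-Seq comparison, with a coefficient of variation of 0.4, alpha 0.05 and power 0.8, "a sample size of 20 per group will be needed". No power is given for strata within EE.
- **Same measures elsewhere.** In Gut microbiota/microbiome, the bacterial strains sought are those "whose representation/abundance are correlated with severity of EE (as assessed by histologic grading"). The Data analysis plan treats growth z-scores both as continuous and as categorised, and lists wasting severity and histologic severity among the variables for the MaAsLin linear models of microbial features.

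**The concern.** CRP, rotavirus IgA level and growth z-scores are continuous. The EE score combines several histologic features and is meant to describe a spectrum. Forming strata from them treats children just either side of a cut as different and children at opposite ends of one stratum as alike. With so few biopsied children, that costs power. With no cut-points stated, the gene list would also depend on where the cuts are later placed.

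Within-EE contrasts are valuable here because they avoid the Pakistan v US difference built into every comparison with the US control groups, and because the article seeks biomarkers of disease severity. It would be a pity to run them with the weaker of two available methods, when the microbial analyses in the same children already use severity in correlations and linear models.

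**Working it through.** **1. The article's own RNA-Seq figure.** The usual count-data formula is n per group = 2(z_a + z_b)²(1/depth + CV²)/(ln FC)². CV 0.4, alpha 0.05 and power 0.8 are stated. Depth and fold change are not. Assuming 20 counts per gene and a 1.5-fold change: 2 × (1.960 + 0.842)² × (0.05 + 0.16)/(0.4055)² = 15.70 × 0.21/0.1644 = 20.05. The figure of 20 is reproduced, but only under those two assumptions. Step 4 needs neither of them.

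**2. Information kept by a two-way cut.** For a normal measure cut so that a fraction p lies on one side, the fraction kept is φ(z_p)²/[p(1 − p)].
- Median: 0.1592/0.25 = 0.64, so 36% is lost
- One-third cut: 59% kept
- One-quarter cut: 54% kept
- One-fifth cut: 49% kept

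For weak effects, a median split of 50 children is worth about 0.64 × 50 = 32 children analysed at full scale, and a split of 25 about 16.

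**3. Power by simulation.** 20,000 datasets per setting, with a normal measure and a linear relation to expression. The test of the correlation at full scale is compared with a t test between median halves, both two-sided. The correlations (r) are assumptions, since the article gives none. Alpha 0.001 is a stand-in for a stricter FDR-type threshold and is not in the article.

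| n | r | Alpha 0.05: full v split (loss) | Alpha 0.001: full v split (loss) |
|---|---|---|---|
| 25 | 0.3 | 31.6% v 21.1% (10.5) | 2.8% v 1.2% (1.6) |
| 25 | 0.4 | 52.6% v 34.4% (18.2) | 8.4% v 3.1% (5.3) |
| 25 | 0.5 | 74.5% v 51.7% (22.8) | 21.9% v 7.4% (14.5) |
| 25 | 0.6 | 91.5% v 71.6% (19.9) | 47.1% v 16.7% (30.4) |
| 50 | 0.3 | 57.3% v 38.9% (18.4) | 11.6% v 4.9% (6.7) |
| 50 | 0.4 | 83.8% v 63.9% (19.9) | 34.9% v 14.2% (20.7) |
| 50 | 0.5 | 96.8% v 84.7% (12.1) | 68.0% v 33.0% (35.0) |
| 50 | 0.6 | 99.8% v 96.0% (3.8) | 92.6% v 61.2% (31.4) |

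At n = 50, r = 0.7 and alpha 0.05 the loss is 0.3 points. Uneven cuts cost more: at n = 25, r = 0.5 and alpha 0.05, a 20/80 split has 39.9% power.

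**4. Against the article's 20 per group.** For a two-sided t test at alpha 0.05, 20 v 20 has 80% power at a standardised difference of d = 0.909. Holding d fixed:
- 12 v 13 (25 children): noncentrality 0.909 × √(12 × 13/25) = 2.27 on 23 df, power 59%
- 25 v 25 (50 children): noncentrality 0.909 × √(25 × 25/50) = 3.21 on 48 df, power 88%

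**The case against.** The strongest reply is that the sub-stratification is called potential, that it serves neither the primary comparison (IFNγ and APOA1, EE v healthy controls) nor the secondary one (undirected, between the described groups), and that cut-points for an exploratory analysis belong in a fuller document. This stands as to weight, and missing cut-points are not held against the article. It does not remove the point, because the article does name a method, comparison of strata, and that choice can be improved.

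Three stronger readings are tempting and are not supported:
- **That most of the information is thrown away.** A median split keeps 64%. The loss passes half only at about 20/80 or more extreme, and no cut is stated.
- **That the strata must fall below 20 per group.** The Data analysis plan treats children with and without infection as parts of one EE group, so about 50 children may be split, giving 25 v 25. The shortfall arises only if the strata are formed among the 25 infection-free children.
- **That no recognised cut exists.** The Data analysis plan cites the WHO Child Growth Standards with z-score cuts at −2, and Study settings and participants separates moderate from severe malnutrition at WHZ −3.

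The simulation also used t tests and linear regression on normal data, not the Audic Claverie method. Biopsied children are restricted to refractory wasting, so WHZ is truncated among them. The EE score was still being developed, so the cost of cutting it depends on its final levels. These limits apply to the exact figures. The direction of the loss does not hinge on them if the relation is roughly monotone and near-linear.

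Finally, the abstract and the deep-learning paragraph mention other ways to relate histology to gene expression, so these strata are not the only route. Neither place states a per-gene test of these measures at full scale.

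**Conclusion.** The point holds as a cheap improvement to a potential exploratory analysis. Comparing strata cut from CRP, histologic severity, rotavirus IgA and growth loses about 36% of the information at a median split, and more at uneven cuts. For assumed correlations of 0.3 to 0.5, a normal measure, a linear relation and nominal alpha 0.05, the cost is about 11 to 23 points of power with 25 children and 12 to 20 with 50. With 50 it fades towards zero as the correlation strengthens.

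A reader might take one large loss from the table, such as 35 points at n = 50, r = 0.5 and alpha 0.001, as the cost of the plan. The documents do not support this: both the correlation and that alpha are assumptions. At stricter thresholds the loss can be larger or smaller depending on the effect; at n = 25 and r = 0.3 it is under 2 points, because neither method has useful power there.

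If only the 25 infection-free children are split, 12 v 13 misses the article's own 20 per group and gives about 59% power for the effect that 20 per group detects with 80%.

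**What to change.** In the RNA-Seq part of the Data analysis plan, make the main within-EE test a per-gene regression that accepts continuous covariates, such as a negative-binomial or voom/limma model. Enter one measure at a time, with age and sex as covariates:
- log CRP
- the EE histology score, continuous or ordinal according to its final levels
- rotavirus IgA level
- WHZ and HAZ, or their change

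Apply Benjamini-Hochberg FDR 0.05 to the slope. Keep strata for display, for established WHO categories, and for infection identified or not, which is truly binary. State whether these analyses use all EE children or only the infection-free ones.

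The cost is a change of wording and analysis code, with the same sequencing data and no extra samples. The downside is that a slope assumes a roughly monotone, near-linear relation on the log-expression scale, to be checked with a plot or spline, and it is a little harder to display than a two-group fold change.
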